### Covariables

- Family structure and relations, determined by the genogram technique [53].

- Perceived pain threshold and tolerance (count of positive tender points and determination of the pain threshold and tolerance using a pain meter).

- Sociodemographic variables: age, sex, race, education level, profession, income level, weight (kg), and height (cm).

- Dependence on tobacco, alcohol or other pyschoactive substances.

- Any present comorbidity.

- Diagnostic characteristic variables, according to traditional Chinese medicine.

### Data storage and confidentiality

All questionnaires are stored in a locked cabinet in a locked room at each participating centre, and have a unique identification number. Consent forms are stored separately from study questionnaires in a locked cabinet. Only anonymised data are entered into the computerised study database, and access to the database is restricted to the study team.

### Statistics

The statistical analysis will be carried out for two types of groups: (1) per intention to treat, with all patients randomised; (2) per protocol, including only patients presenting no more than minor deviations from the protocol.

We will compare the baseline variables for the different groups in terms of difference of the means and of proportions. The magnitude of the difference in the possible imbalance produced by the random assignation to the groups will be evaluated using ratios of the means and of proportions (using that of the control group (sham acupuncture) as a reference level, and the final adjustment will be made using secondary analyses with multiple linear regression models, as described below. In the unadjusted analysis, significance tests will be used to compare the sample (parametric or otherwise, depending on the symmetric or asymmetric distribution of the result variables and on the homogeneity of their variances), taking the control group as a reference, using comparison tests for differences of the mean in the main results variable, both as regards inter-group comparisons (for independent samples) and for comparisons between the baseline and final levels for each group (in this case, using tests for non-independent or paired samples).

For the main result variable, pain intensity, we will construct linear regression models, adjusted for baseline level, treatment centre and depression, and using intention to treat analysis. The group variables will be included, taking the control group as a reference, together with the sociodemographic variables (age and sex), together with the baseline variables for severity of the process (pain intensity, FIQ and HAMD) and pain threshold and tolerance. Adjustments will be made for possible confounders, using criteria of statistical significance and confounding. The detection of possible interactions with the treatment group variable will be evaluated using statistical significant criteria for the corresponding interaction terms. P values < 0.05 will be declared to be statistically significant.

For the cost effectiveness analysis, a non-parametric bootstrapping approach will be used with the incremental cost effectiveness preference map to illustrate the willingness to accept: willingness to pay ratio, and a 95% confidence interval will be computed for the different measures of effectiveness [54]. For cost imputation, drug consumption will be taken into account, and different thresholds established for acceptance of the experimental treatment, to evaluate diverse scenarios. For the cost associated with the treatment, the all patients Diagnosis Group Relationship measure will be used, in association with the main diagnosis, together with the average professional salary/hour, and the indirect costs associated with acupuncture sessions.

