### Sample size

The sample size is set at n = 56 patients in each group, for a significance level of 5%, a power of 90% and a difference in the mean pain intensity - according to 0-100 mm VAS - between the real and the sham acupuncture groups of 20.2 points, assuming equal variances (standard deviation = 32.4 points), taking into account the results of an earlier pilot experiment, carried out from April to December 2008. Assuming a dropout rate of 25%, the sample size will thus be n = 75 for each group (n = 78 to adjust by strata). These calculations were performed using the SamplePower 2 program [39].

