### Randomisation

The randomisation of the two branches of this study will be performed in a centralised way, allocating the participants with stratification by centre and depression diagnosis and blocking following a 1:1 allocation ratio. The healthcare professionals participating in the study will not take part in the randomisation process. Those patients who meet the criteria for inclusion and who provide written informed consent will be included in the study. Following their inclusion, the researcher will contact the randomisation centre where the patient is registered, and the physician will be informed, by telephone and by fax, of the patient's assignation to one of the two study branches. This procedure ensures that the randomisation is not influenced by the researchers taking part in this study.

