### Outcomes

#### Primary outcome

Changes in pain intensity, measured on a visual analogue scale, at the end of treatment. The construction validity and reliability of this scale have been proven in previous studies [41-43]. The scale measures a continuous quantitative variable varying from 0 (absence of pain) to 100 (the worst pain imaginable).

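### The primary 10-week pain comparison has two between-group analyses of inconsistent status, and the plan does not say which one decides the trial

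*Protocol article*

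**What the plan says.** The Primary outcome section defines a single endpoint, "Changes in pain intensity, measured on a visual analogue scale, at the end of treatment". The Sample size section powers a two-group comparison of means, "for a significance level of 5%, a power of 90% and a difference in the mean pain intensity". The Statistics section then gives several analyses of that endpoint:

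- **Unadjusted between-group test.** It is applied to the main outcome, and its type is "parametric or otherwise, depending on the symmetric or asymmetric distribution of the result variables and on the homogeneity of their variances".
- **Paired tests within each arm.** The same sentence adds "comparisons between the baseline and final levels for each group".
- **Regression.** On dealing with chance imbalance the section says "the final adjustment will be made using secondary analyses with multiple linear regression models, as described below". The next paragraph says "For the main result variable, pain intensity, we will construct linear regression models, adjusted for baseline level, treatment centre and depression", by intention to treat. It also lists age, sex, baseline FIQ and HAMD, and pain threshold and tolerance. Further confounders may enter according to statistical significance and their confounding effect.
- **Decision rule.** "P values < 0.05 will be declared to be statistically significant". The sentence is not tied to any one of these analyses.

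The Randomisation section describes "allocating the participants with stratification by centre and depression diagnosis and blocking following a 1:1 allocation ratio". The Discussion says that the main analysis is by intention to treat. That fixes the population but not the test.

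**The concern.** The regression models are labelled secondary in one paragraph, and in the next they are the models specified for the main outcome. Between the two labels stands an unadjusted test of the same outcome. If one gives p = 0.04 and the other p = 0.07, the article offers no rule for which result counts.

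Neither route is fully fixed. The unadjusted test can move from a comparison of means to a rank comparison once the outcome has been seen, and this changes what is estimated. The regression can gain covariates by their significance. The unadjusted test also leaves out both factors that stratified the randomisation, and it does not adjust for baseline VAS, which is collected at T0. What is at stake is the error rate of the primary claim and whether a later choice of analysis can be checked against the published plan.

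**Working it through.** **1. The plan's own sample size.** Inputs from the Sample size section: difference 20.2, SD 32.4, alpha 5%, power 90%, dropout 25%.

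- Normal approximation: n = 2 × (1.960 + 1.282)² × 32.4² / 20.2² = 54.1, so 55 per arm.
- Noncentral t: power is 0.8998 at 55 and 0.9049 at 56, so 56 is the first n to reach 90%.
- A one-sided 5% level would give 45, so the plan's figure is two-sided.
- Dropout: 56 / (1 − 0.25) = 74.7, so 75.

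Both stated figures, 56 and 75, reproduce.

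**2. The status of each analysis, side by side.**

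| Analysis of 10-week pain | Status in the article | Left open |
|---|---|---|
| Unadjusted between-group test | Described first; never called primary | Parametric or rank, from the outcome data |
| Adjusted regression | Secondary in one paragraph; the model for the main outcome in the next | Extra covariates, partly by significance |

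The Sample size section fits the unadjusted test of means but does not name it as the deciding test.

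**3. Error rate if either result could be claimed.** Null simulation: 56 per arm, normal data, 10,000 runs per correlation. The adjusted model contains arm and baseline only. The correlation r between baseline and final VAS is not in the document and is assumed.

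| Probability of p < 0.05 under the null | r = 0.3 | r = 0.5 | r = 0.7 |
|---|---|---|---|
| t-test alone | 4.7% | 5.0% | 5.3% |
| Adjusted model alone | 4.8% | 5.3% | 5.0% |
| t-test or adjusted model | 6.0% | 7.6% | 8.4% |

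A second simulation followed the stated procedure more closely. It chose between t-test and Mann-Whitney by Shapiro and Levene tests (these selection rules are an assumption). The selected test or the adjusted model was significant in 6.1%, 7.3% and 8.7%. If the unadjusted t-test is run on change from baseline instead of the final score, that test or the adjusted model gives 7.3%, 7.8% and 6.6%. All of these lie between about 6% and 9%. None includes data-driven covariate selection.

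**4. Power at the planned difference.** SD 32.4 is read as the SD of the 10-week score. The standard error is 32.4 × √(2/56) = 6.12 unadjusted, and 6.12 × √(1 − r²) after baseline adjustment. Power ≈ Φ(20.2/SE − 1.960).

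| | SE | 20.2/SE | Power |
|---|---|---|---|
| Unadjusted | 6.12 | 3.30 | 91.0% (90.5% by noncentral t) |
| Adjusted, r = 0.3 | 5.84 | 3.46 | 93.3% |
| Adjusted, r = 0.5 | 5.30 | 3.81 | 96.8% |
| Adjusted, r = 0.7 | 4.37 | 4.62 | 99.6% |

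Naming the adjusted model as primary needs no more patients.

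**The case against.** The strongest reply is that a hierarchy can be inferred. If adjustment is secondary, the unadjusted test leads, and the sample size is built on exactly that comparison. The article also condenses a fuller plan. Part of this stands: the unadjusted reading is possible, and one sentence would settle the matter. It does not remove the conflict, because the next paragraph gives the main outcome an adjusted intention-to-treat model. The fault lies in what the article states, so it is more than detail left to an analysis plan.

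A reader might also infer stronger faults that the document does not support:

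- **Choosing the test from the data inflates the error by itself.** In simulation on normal data, the selected test alone stayed at about 4.8–5.2%. The inflation comes from having two candidate analyses. Counting t-test, Mann-Whitney and adjusted model together would overstate it, because the plan runs one unadjusted test.
- **The trial is underpowered without adjustment.** At the planned 20.2 mm the unadjusted test meets the 90% target. Adjustment is a gain in precision and does not repair a shortfall.
- **The 5% rule licenses claims on every secondary outcome.** The sentence closes the paragraph on the main outcome and its interactions and does not mention secondary outcomes. Multiplicity there is commonly left to the analysis plan.
- **A within-arm change will be claimed as benefit.** The Hypothesis section requires more pain reduction than under sham, and the Discussion expects that sham may have some effect. The paired tests add nothing to the randomised comparison, but nothing shows that they would be used as proof.

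**Conclusion.** The point holds as an inconsistency in the status of two between-group analyses of the primary outcome, each partly dependent on the data, with no statement of which decides. An error of about 6–9% instead of 5% is a worst case. It assumes that whichever result is positive would be claimed, which the document does not say, and it rests on normal data and assumed correlations of 0.3 to 0.7. The sample size is not in error. The adjusted analysis is the better choice for primary: it uses the baseline value and strata already collected, and at the planned difference it keeps at least the planned power at every correlation tried.

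**What to change.** In the Statistics section, name one primary analysis: an intention-to-treat ANCOVA of 10-week VAS on arm, baseline VAS, centre and depression stratum, with a fixed covariate list. Report the adjusted mean difference, its 95% confidence interval and a two-sided p value, and tie the 5% rule to that result. Remove the secondary label from this model.

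Label the unadjusted or rank test and any further-adjusted models as supportive. Do not choose the test or the covariates from the outcome data. Report within-arm changes descriptively, not as evidence of effect.

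The cost is a few sentences, with no new data and no more patients. The Study period section says that nobody had yet been recruited, so at that point the choice could be fixed before any outcome was seen. The downside is less freedom of analysis after the data are seen.

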#### Secondary outcomes

- Changes in levels of depression, measured on the Hamilton hetero-evaluation scale, at the end of treatment and after 6 months. This scale is of proven discriminant validity, reliability, and sensitivity to change; moreover, it has been validated for use in Spain [44]. It consists of 17 items. Each question has from three to five possible responses, with scores varying from 0-2 to 0-4, respectively. The total score varies from 0-52. To evaluate the response to treatment, a full response is defined as a reduction of 50% or more in the initial score obtained on the scale; a partial response is taken as a reduction of 25-49%, and absence of response is defined as a reduction of less than 25%. Remission is considered to have been achieved with a score of 7 or less, although according to some studies this cut-off point should be lower [45].

- Changes in the overall indicator value and in the different subscales of the Spanish version of the Fibromyalgia Impact Questionnaire [46], at the end of treatment (10 weeks after the start), and at 6 and 12 months from the start of treatment. This is a self-administered questionnaire that measures the aspects of health most affected by FMS during the previous week [47]. It is comprised of ten items, with three questions valued on a Likert scale, and a further seven questions valued on a visual analogue scale, varying from 0 to 10, with the higher scores reflecting a greater negative impact or more severe symptoms.

- Changes in pain intensity on a visual analogue scale, measured at the end of treatment, and at 6 and 12 months after beginning treatment.

- Changes in the pain threshold and number of tender points detected by experienced evaluators, assigned one per centre and non-interchangeable, using a digital pressure algometer with a contact point of 1 cm^2 ^(NIDEC SHIMPO - FGE-100 X - Digital Force Gauge). The pressure applied is 1 kg/s at each of the 18 tender points specified [48]. The patients will be asked to tell the researcher when the sensation of pressure changes to one of pain. From all of these pain points, a mean threshold will be calculated. Normal subjects begin to perceive pain at a pressure of 4 kg [38]. The baseline measurements will be compared with those obtained at the end of treatment, and after 6 and 12 months.

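### Beyond a named core, covariates in the pain regression are added by statistical significance and observed confounding, and unnamed treatment interactions are screened at 0.05; one closed model and one named interaction should replace this

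*Protocol article*

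**What the plan says.** The relevant text is in the Statistics section of the protocol article.

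- **Core set.** The linear regression for pain intensity is to include baseline pain, centre, depression, age, sex, FIQ, HAMD, and pain threshold and tolerance.
- **Additions.** A further rule follows: "Adjustments will be made for possible confounders, using criteria of statistical significance and confounding". It comes with no candidate list, entry threshold or definition of confounding. The Covariables section offers a wide pool, including family structure, education, income, weight, comorbidity, substance dependence and the traditional Chinese medicine diagnosis.
- **Interactions.** "The detection of possible interactions with the treatment group variable will be evaluated using statistical significant criteria for the corresponding interaction terms". None is named. The section's general threshold is P < 0.05, and it states no adjustment for the number of interactions tested.
- **Imbalance.** "The magnitude of the difference in the possible imbalance produced by the random assignation to the groups will be evaluated using ratios", with the final adjustment left to regression models that this sentence calls secondary. The next paragraph presents the same models as the intention-to-treat analysis of the main outcome.
- **Unadjusted test.** This may be parametric or not, depending on the observed distribution and variances.

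The Randomisation section states central 1:1 allocation, stratified by centre and depression diagnosis.

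**The concern.** Central stratified randomisation makes baseline differences at allocation a matter of chance. A search for confounders in the observed data therefore has no clear purpose. Covariates earn their place because they were stratification factors or predict the outcome, and both can be settled in advance. A rule based on significance or observed confounding makes the final adjusted pain effect depend on the data it summarises, and two analysts could follow it and reach different models.

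This sits beside two other open choices: an unadjusted test whose type depends on the data, and a regression described as secondary in one place and as the main-outcome analysis in another. Several results could be presented as the trial's answer.

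For interactions, screening an unspecified number of terms at 0.05 invites chance findings in a trial sized only for the overall difference. The one interaction that the design points to is treatment by depression: depression is a stratification factor and appears in the Hypothesis. It is not singled out.

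**Working it through.** **1. The plan's own figure.** The Sample size section gives "for a significance level of 5%, a power of 90"%, a difference "between the real and the sham acupuncture groups of 20.2 points", and "assuming equal variances (standard deviation = 32.4 points" on the VAS. The number of sides is not stated; two-sided is assumed.

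- Normal approximation: n = 2 × (1.960 + 1.2816)² × (32.4 / 20.2)² = 2 × 10.507 × 2.573 = 54.1, so 55 per group.
- t-based solution: 55.04, so 56 per group, which matches the stated figure. One-sided would give 45.
- Dropout: 56 / 0.75 = 74.7, so 75. The plan then rounds to 78 for strata, 156 in total.

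The sample size reproduces and is not in question. It fixes the simulation sizes: 112 (2 × 56) and 156 (2 × 78).

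**2. Effect of covariate selection on type I error.** Null simulation, 4,000 runs per setting. The outcome is 0.5 × baseline + 0.2 × each of k independent candidates + unit noise, with no treatment effect. k is 8 or 12. The number and strength of candidates and the 10% change-in-estimate threshold are assumptions, because the document gives none.

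| Analysis rule | Type I error for treatment (nominal 5%) |
|---|---|
| Fixed model (treatment and baseline) | 4.8 to 5.4% |
| Keep candidates with p < 0.05 | 5.8 to 7.0% |
| Keep candidates that change the estimate by more than 10% | 4.4 to 4.8% |
| Keep on either criterion | 5.2 to 6.1% |
| Smallest p among five regressions (baseline-only, full, three selected) | 8.4 to 10.2% |

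The simulation standard error near 5% is √(0.05 × 0.95 / 4000) = 0.0034, so about ± 0.7 points.

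A second null simulation (112 patients, baseline plus 10 correlated candidates, 4,000 runs) gave 5.4% for significance-based selection and 4.9% for the 10% rule. It gave 11.5% when any of the unadjusted, rank, ANCOVA or selected analyses could be reported. The two sets together give about 4 to 7% for one rule, and roughly 8 to 12% for free choice.

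**3. Interactions.** With k independent tests at 0.05, the chance of at least one false positive is 1 − 0.95^k:

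| k | 1 | 3 | 5 | 8 | 10 | 12 |
|---|---|---|---|---|---|---|
| Chance | 5% | 14% | 23% | 34% | 40% | 46% |

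The first simulation agreed: about 34% for 8 candidates and 46 to 47% for 12.

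**The case against.** The strongest reply is that the plan already fixes most of the model. That is right: the core contains both stratification factors, and the selection rule governs only what is added. A reader might infer that the data choose all the covariates; the text does not say so.

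Second, a reader might conclude that the reported p value and interval are invalid. The simulations do not support this for a single rule applied mechanically, where inflation is small or absent. The 8 to 12% comes from free choice among analyses. Deleting the selection sentence alone would not remove that, because the unadjusted, rank and regression results would remain side by side with none named primary.

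Third, the interaction figures need a number of tests that the document does not give. Treating every core covariate as tested would yield 1 − 0.95⁹ = 37%, but the text does not say that each is tested, and independence is doubtful: the depression stratum is HAMD cut at 21. Nor does the plan promise subgroup conclusions.

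Fourth, the plan assumes 25% dropout, and the Discussion recognises possible differential losses, so imbalance among completers need not be pure chance. This stands, but selection by significance is no remedy for it.

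Fifth, the Ethical considerations section has third parties analyse the data without knowing their origin. This limits steering towards acupuncture. It does not stop the model from depending on the data, since coded groups still have outcomes and p values.

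Two further readings are tempting and not supported. One is that pain threshold, remeasured after treatment, might enter the model as a post-treatment value. It is listed directly after the baseline severity variables, appears under Covariables and has a baseline measurement in Table 2, so nothing indicates this. The other is that tolerance is never measured, because the outcome procedure records only the onset of pain ("The patients will be asked to tell the researcher when the sensation of pressure changes to one of pain") and Table 2 has no tolerance row. The Covariables section provides for it ("count of positive tender points and determination of the pain threshold and tolerance using a pain meter"), and a condensed article may omit the procedure.

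**Conclusion.** The point holds in a limited form and should be fixed. The protocol states a rule that makes additions to the main-outcome regression depend on the data, and it screens unnamed interactions at 0.05. A later analysis plan that followed this text would inherit both. Under the assumed candidates, the rule alone costs at most about two percentage points of type I error. The larger exposures are the absence of one settled primary analysis (roughly 8 to 12% if the choice is free) and open interaction testing (about 34 to 46% for 8 to 12 independent tests, less if they are positively correlated). These sizes are illustrative. That the rule is data-driven, and that no interaction is named, rests on the text alone.

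**What to change.** 1. Delete the sentence on adjusting for possible confounders.
2. Name one primary analysis: an intention-to-treat linear model for VAS pain at 10 weeks, with treatment, baseline VAS, centre, depression stratum, age and sex. All covariates take their T0 values and are kept whatever their p values.
3. Label the unadjusted comparison as a sensitivity analysis. Label as a second one a model adding the other named covariates at T0 (FIQ, HAMD, pain threshold and tolerance). Remove the conflicting description of the regressions as secondary.
4. Prespecify treatment by depression stratum as the only formal interaction test, and call any others exploratory.

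The cost is wording. The sample size stays at 56, then 75, then 78 per group, one fixed model keeps type I error near nominal (4.8 to 5.4% in simulation), and one named interaction carries a 5% false-positive chance. The Study period section reports that no patients had been recruited, so on that footing the change can precede all data. The downside is that a striking chance imbalance in another variable could be adjusted for only in a sensitivity analysis.
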